### Outcomes

The primary outcome of this study will be:The difference in change in HADS score between the intervention and conservative group at 12 months.

The secondary outcomes of this study will be:The difference in change in the CollaboRATE shared decision-making survey score and CSQ score between the intervention and the conservative groups at 12 months.Provider exit survey responses at 12 months.

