### Sample size

Using the validation information in our previous study [23] and the following assumptions of 80% power and a two-sided alpha of 0.05, a total sample size of 356 (178 in each group) will be required to detect effect of 0.298 difference between the intervention and the conservative groups. The same size has been calculated for both HADS-Anxiety score (HADS-A) and HADS-Depression score (HADS-D) by the independent T-test. This study will use the sample size calculated for HADS-A, as it required a larger sample size and to ensure there will be sufficient power for both HADS-A and HADS-D. This sample size will be inflated by 10% to 392 (196 in each group) to account for possible dropouts, losses to follow-up, and withdrawals of consent.

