The primary outcome of difference in change of HADS-D and HADS-A, from baseline to 12 months between the intervention and conservative groups, will be tested using an independent T-test. The change of HADS score will be tested by MANOVA for two-way design setting to check if a statistically significant mean of change exists through time points between the groups. The MANOVA helps control for inflation of Type I error (rejection of a true null hypothesis as the result of a test procedure) and count the correlation between sections. Post-hoc Tukey Honestly Significant Difference (HSD) Test will be performed afterwards with adjustment by Bonferroni method, which allows many comparison statements to be made while still assuring an overall confidence coefficient is maintained. Paired T-test will also be considered for use. Regression analysis will be performed to quantify the change of CSQ through time points and between the groups considering patients’ individual effect as random effect. With more than 10% cumulative missing rate, the last observation will be carried forward in the case of missing data. The difference in change in both CSQ score and CollaboRATE shared decision-making survey score, will be analysed using the same methods as described above. The CSQ will be treated as continuous variables with an overall satisfaction score as a sum of the sub-scales for each question in the CSQ.

Linear mixed effect model will be used in multivariable analysis level in order to adjust patients’ individual effect and to quantify the change of outcome measure through time points and between the groups considering the impact of selected variables when they cooperate by presenting the coefficient (standard error), 95% confidence interval, and *P*-values. The variables included in the multivariable analysis will be selected if they were statistically significant on the univariate level analysis and considered clinically significant by the research team.

For provider exit surveys, mean and median values will be calculated from questions assessed on a Likert scale. Proportion of responses on each multiple choice answers will be determined on the one multiple choice question. Open ended responses will be assessed qualitatively.

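### The post-hoc HADS step puts a Bonferroni adjustment on Tukey HSD, a redundant correction if both cover the same pairs, and does not target the difference in change; the primary t-test is unaffected (minor)

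*Protocol article*

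**What the plan says.** The primary outcome in the Outcomes section is: "The difference in change in HADS score between the intervention and conservative group at 12 months". Data analysis tests it for HADS-D and HADS-A by an independent t-test and attaches no multiplicity correction to that test. The Sample size section plans for the same test, with "80% power and a two-sided alpha of 0.05", and arrives at 178 patients per arm for an effect of 0.298.

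Data analysis then adds a two-way MANOVA on the change of HADS score across time points and groups, and continues: "Post-hoc Tukey Honestly Significant Difference (HSD) Test will be performed afterwards with adjustment by Bonferroni method". The reason given is that this "allows many comparison statements to be made while still assuring an overall confidence coefficient is maintained". The text does not say which means are compared, how many comparisons there are, or whether Bonferroni runs over the pairs or over the two subscales. CSQ and CollaboRATE are to be analysed by the same methods, so the step may reach the secondary outcomes too.

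**The concern.** Tukey HSD is itself a simultaneous procedure for all pairwise differences, and the reason the plan gives for the combination is one that Tukey meets alone. A second correction over the same pairs costs power and buys nothing.

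The contrasts are also in doubt. The question is a difference of differences: (intervention at 12 months − intervention at baseline) − (conservative at 12 months − conservative at baseline). A pairwise comparison of group-by-time cells sets one arm against the other at one visit, or one visit against another within an arm. Neither is that quantity.

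At stake is how the post-hoc HADS results, and possibly those for CSQ and CollaboRATE, can be read. The analyst would also have to choose the family and the contrasts later, because the sentence does not fix them.

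**Working it through.** **Inputs from the protocol.** 178 per group, two-sided alpha 0.05, 80% power, effect 0.298 (Sample size); 1:1 allocation, the intervention arm measured at 0, 6 and 12 months and the conservative arm at 0 and 12 (Design).

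**Assumptions.** 0.298 is in SD units of change, since no SD is given. There are four cells (two arms, two shared visits) of 178, and expected baseline means are equal by randomisation. Within-patient correlation ρ is 0.5 to 0.8.

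**1. The plan's own figure.** Noncentrality = 0.298 × √(178/2) = 2.81. With 354 df and critical t 1.967, power is 80.06%; at 177 per group it is 79.84%. So 178 per group is reproduced, which supports reading 0.298 as a standardised difference.

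**2. Critical values, four cells.** Pairs = 4 × 3/2 = 6; df = 4 × 177 = 708. The critical t is the studentised-range quantile divided by √2.
- Tukey alone (0.95 quantile): 2.575.
- Tukey with Bonferroni over two subscales (0.975 quantile): 2.825.
- Tukey with Bonferroni over six pairs (1 − 0.05/6 quantile): 3.181. The family-wise error becomes 0.05/6 = 0.0083, about 0.8%.

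**3. Power of the 12-month between-arm cell contrast.** An effect of 0.298 SD of change equals 0.298 × √(2(1 − ρ)) in SDs of the score, because SD of change = SD of score × √(2(1 − ρ)).

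| ρ | Effect (score SD) | No correction | Tukey | Tukey + Bonferroni over 2 subscales | Tukey + Bonferroni over 6 pairs |
|---|---|---|---|---|---|
| 0.5 | 0.298 | 80% | 59% | 50% | 36% |
| 0.6 | 0.267 | 71% | 48% | 38% | 25% |
| 0.7 | 0.231 | 58% | 35% | 26% | 16% |
| 0.8 | 0.188 | 43% | 21% | 15% | 8% |

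The second correction is the move from the Tukey column to one of the last two. The fall down the no-correction column comes from the choice of contrast and ρ, not from any correction. With five cells (adding the intervention arm's 6-month visit; 10 pairs) and ρ = 0.5, Tukey gives 53% and full stacking 26%.

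**4. Repeated measures.** Tukey HSD for independent cells takes the SE of any pair as SD × √(2/n). For two visits of the same patients it is SD × √(2(1 − ρ)/n). The SE used for a within-arm pair is therefore too large by a factor 1/√(1 − ρ): 1.41 at ρ = 0.5 and 2.24 at ρ = 0.8.

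**5. If change is the response.** The conservative arm has no 6-month measurement, so each subscale has one between-arm comparison at 12 months. With two means, Tukey's critical value is the ordinary 1.967 and power is 80%: it corrects nothing. If the intervention arm's 6-month change is added as a third mean (treated as independent), Tukey gives 68%, and Bonferroni over the three pairs on top gives 52%.

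**The case against.** The best defence is that the sentence is loose rather than wrong. It never mentions cell means, and the sentence before it makes change the response, in which case the between-arm comparison at 12 months is the difference in change. Bonferroni may be meant only for HADS-A and HADS-D, a defensible use. The primary t-test stands apart from this step, and a patient-level mixed model with confidence intervals is already planned.

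Much of this stands. The cell-mean reading is an inference, although the two-way design and the reference to group differences at the different time points make it likely. The Bonferroni family is open. The primary inference is untouched.

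Four stronger conclusions that a reader might draw are not supported:
- That the double correction removes most of the power. Against Tukey alone, full stacking loses 40% of it at ρ = 0.5 (59.3% to 35.7%) and about 47% at 0.6. The loss passes half only at higher correlations.
- That the 8% to 36% range can be set against the primary test's 80% as the cost of stacking. Part of that gap is due to Tukey itself, the contrast and ρ.
- That the stated confidence coefficient is wrong. No number is stated, and a conservative procedure still keeps at least the nominal level.
- That significant within-arm contrasts under a shared time trend are false positives. A real trend makes those contrasts truly non-zero; they just do not answer the trial's question.

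The defence does not rescue the step. If change is the response, Tukey has nothing to do at 12 months, and only a correction across subscales could be of use.

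**Conclusion.** The concern holds as a minor fault in a supportive analysis. Depending on the reading, the prescribed combination over-corrects, compares means that do not give the difference in change, or leaves Tukey idle. With full stacking over six pairs, it costs about 24 points of power against Tukey alone at ρ = 0.5 (59% to 36%) and about 13 at ρ = 0.8 (21% to 8%). With Bonferroni over the two subscales only, it costs about 7 to 10 points.

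These figures rest on four cells of 178, a standardised effect of 0.298 and an assumed correlation range, none of which the protocol fixes for this step. The error is on the conservative side. The sample size and the primary t-test at 80% power are unaffected; CSQ and CollaboRATE are affected only if the post-hoc step carries over to them.

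**What to change.** Delete the Tukey-plus-Bonferroni sentence. Follow the overall HADS test by one contrast per subscale, the between-arm difference in 12-month change, with its confidence interval, from the patient-level mixed model already in the plan. If multiplicity across HADS-A and HADS-D is to be handled at this step, name a single correction over those two tests, for example Holm. Report within-arm changes as descriptive estimates. State whether the same rule applies to CSQ and CollaboRATE.

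This changes a sentence or two of analysis text and needs no new data and no change to the sample size. The downside is fewer post-hoc p-values.

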**Fig. 1 Fig1:**
[figure not shown]
Study protocol timeline and flow chart. MS, multiple sclerosis; PROMs, patient reported outcome measures; CSQ; consultant satisfaction questionnaire

Participants are randomly assigned in a 1:1 ratio to one of two groups:*Intervention group*: All participants randomized to the intervention group will be asked to complete the following validated questionnaires at baseline and approximately every 6 months for a total of 12 months:Hospital Anxiety and Depression Scale (HADS) score [24]Quality of life as measured by EuroQol five-dimensional questionnaire (EQ5D) [25]Fatigue as measured by Modified Fatigue Impact Scale (MFIS) [26]The Patient Determined Disease Steps (PDDS) [27]Patient Health Questionnaire-9 (PHQ-9) [28]Open ended text response to (limit 280 characters) “What are the top 3 things you would like your MS healthcare provider to know about you right now?” – to be referred as the 3-item prompt (3IP). Completed questionnaires will be sent to the treating provider via a secured link using encrypted email to review the corresponding scores and the text response to the 3IP.*Conservative group*: All participants randomized to the conservative group will be asked to complete the same questionnaires as above, however only at baseline and at the end of the study at 12 months. Additionally, the treating provider will only be prompted to review the text response to the 3IP and will not be able to access the PROM questionnaire scores.

For both groups, providers will be able to document via REDCap whether they have reviewed the aforementioned items and their response/intervention, if applicable (Supplementary Fig. 3). Examples of provider responses would be phone calls to patients, scheduling earlier appointments, alterations to medication regimens, referral to another health or medical provider, and/or messaging the patient via secure email messaging system; a free text response will also be included to allow documentation of alternative interventions if required. Due to initial lack of provider engagement, providers will be incentivized with token of appreciation ($10 Amazon gift card) for each instance of documenting they have reviewed (and if applicable, enacted healthcare provider intervention in response to) their patients’ PROM scores and/or text responses to 3IP. There will be no difference in incentive if providers offer an intervention (eg. telephone call, referral to another healthcare provider or service, etc.).

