Additionally for both groups, critical absolute scores or decrement in subsequent scores as measured by the aforementioned questionnaires will trigger an automated secured email alert to the patient’s treating MS provider. Critical scores and absolute change in scores considered to be meaningful were determined via analysis of normative data associated with individual PROMs (in a validated population of MS patients when available) (see Supplementary Appendix 1).

All groups will also be asked to complete the Consultation Satisfaction Questionnaire (CSQ) [29] as a measure of provider satisfaction, and the CollaboRATE survey [30] as a measure of shared decision-making, at baseline, and at end of the study at 12 months. At the end of the study, providers will be asked to complete a Provider Exit Survey in regards to their own perception on usage of the study measures in PwMS (Supplementary Fig. 4).

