### Data collection

The questionnaires will be delivered electronically to the patient at baseline for both conservative and intervention groups. For patients in the intervention group, questionnaires will be delivered electronically again at 6 months and at the end of the study at 12 months; in the conservative group, questionnaires will be delivered electronically again at the end of the study at 12 months. Initial CSQ and CollaboRATE surveys will be sent to both groups at baseline and at the end of the study. Patients will be sent an email to ask them to complete the questionnaires, with 2 follow-up reminders (1 week and 2 weeks) after the initial electronic contact. For provider exit surveys, mean and median values will be calculated from questions assessed on a Likert scale. Proportion of responses on each multiple choice answers will be determined on the one multiple choice question. Open ended responses will be assessed qualitatively.

Study methods, data management, and biostatical support is supplied by EPICORE Centre, Department of Medicine/Pharmacology, Faculty of Medicine and Dentistry (www.epicore.ualberta.ca). Data for the study will be collected and managed using REDCap at the University of Alberta. REDCap is a secure, web-based software platform designed to support data capture for research studies, providing 1) an intuitive interface for validated data capture; 2) audit trails for tracking data manipulation and export procedures; 3) automated export procedures for seamless data downloads to common statistical packages; and 4) procedures for data integration and interoperability with external sources [31, 32]. Data from administered PROMs through REDCap will allow for centralized data collection capable of export for future analysis.

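### Last observation carried forward imputes a 6-month HADS change in the intervention arm but zero change in the conservative arm, which biases the primary comparison whenever mean HADS drifts over time

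*Protocol article*

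**What the plan says.** All references are to the protocol article.

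- **Missing data (Data analysis):** "With more than 10% cumulative missing rate, the last observation will be carried forward in the case of missing data". The rule makes no distinction by arm or by outcome. It stands among sentences about the CSQ, but its wording is general.
- **Intervention schedule (Data collection):** "For patients in the intervention group, questionnaires will be delivered electronically again at 6 months and at the end of the study at 12 months".
- **Conservative schedule (Data collection):** "in the conservative group, questionnaires will be delivered electronically again at the end of the study at 12 months". The group descriptions under Design agree: the same questionnaires, "however only at baseline and at the end of the study at 12 months".
- **Primary outcome and test (Data analysis):** the outcome is given as "The primary outcome of difference in change of HADS-D and HADS-A, from baseline to 12 months between the intervention and conservative groups". The test named for it is a two-sample t-test on the change.
- **CSQ and CollaboRATE (Design):** both arms complete these "at baseline, and at end of the study at 12 months".
- **Mixed model (Data analysis):** a linear mixed effect model is named for the multivariable analysis, with covariates chosen partly by univariate significance. It is not the primary test, and it is not exempted from the carry-forward rule.

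**The concern.** Carrying forward the last observation treats two arms alike only if both have the same opportunities to be observed. Here they do not, because the visit schedule is itself part of the treatment contrast. A conservative patient without a 12-month HADS has only a baseline score to carry, so the imputed change is zero by construction. An intervention patient who answered at 6 months contributes a real 6-month change. Randomisation cannot balance this.

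If HADS falls in both arms for reasons unrelated to the intervention, part of that fall is kept in the intervention arm and erased in the conservative arm, which looks like a benefit. If scores rise, the artefact works against the intervention. The quantity affected is the primary outcome.

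**Working it through.** **The plan's own figures.** Sample size assumes "80% power and a two-sided alpha of 0.05" and an effect of 0.298. No SD is given, so 0.298 is read as standardised. The two-sample t-test then needs 177.7, that is 178 per arm, as stated. 356 × 1.10 = 391.6, or 392 (196 per arm), also as stated. The 10% dropout allowance equals the carry-forward trigger, so any loss beyond plan activates the rule.

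**Bias formula.** Let m be the fraction missing at 12 months (equal in both arms, completely at random) and q the share of intervention dropouts with a 6-month score. Let I6 and I12 be the mean intervention changes and C12 the mean conservative change.

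- Expected intervention change: (1 − m)·I12 + m·q·I6
- Expected conservative change: (1 − m)·C12
- Bias of the difference: m·(q·I6 − I12 + C12)

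With no treatment effect, I12 = C12 and the bias is m·q·I6, where I6 is the change common to both arms.

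**Assumed inputs.** The documents give no HADS SD, trend, correlation or value of q. Assumed: subscale SD 4, between-visit correlation 0.65, q = 0.5, 196 per arm, no treatment effect, and the same fall at 6 and 12 months.

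| Missing per arm | Common fall | Bias (points) | Type I error (simulation) |
|---|---|---|---|
| 30% | 0 | 0 | about 5% |
| 12% | 1 | 0.12 × 0.5 × (−1) = −0.06 | about 5.5% |
| 15% | 1 | 0.15 × 0.5 × (−1) = −0.075 | 5.5 to 6% |
| 30% | 1 | 0.30 × 0.5 × (−1) = −0.15 | 8 to 9% |
| 30% | 2 | 0.30 × 0.5 × (−2) = −0.30 | 15 to 18% |

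Ranges cover separate simulation runs. In the same data, the t-test on observed 12-month changes was unbiased, with type I error of 5 to 6%.

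**Check of the last row by hand.** The variance of change is 2 × 16 × (1 − 0.65) = 11.2. With 30% zeros in the conservative arm, its variance is 0.70 × 11.2 + 0.70 × 0.30 × 4 = 8.68. With 15% zeros in the intervention arm, it is 0.85 × 11.2 + 0.85 × 0.15 × 4 = 10.03. The standard error is √((8.68 + 10.03)/196) = 0.309, so the shift is 0.30/0.309 = 0.97 standard errors. The two-sided rejection rate is P(Z > 0.99) + P(Z < −2.93) ≈ 0.16.

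**If every intervention dropout has a 6-month score (q = 1), in units of the SD of change:** 15% missing with a 0.2 SD improvement gives 0.03 SD and about 6%. 30% missing with 0.3 SD gives 0.09 SD (0.09/0.298 = 30% of the target effect) and about 16%.

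**What the schedule difference does not explain.**

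- *Unequal dropout, 15% intervention and 30% conservative, 2-point fall.* Intervention: −2 × (0.85 + 0.15 × 0.5) = −1.85. Conservative: −2 × 0.70 = −1.40. Bias −0.45, type I error about 30%. If no 6-month score is carried, the bias is −1.70 + 1.40 = −0.30, type I error about 17%. So 0.30/0.45, two thirds, is ordinary carry-forward error.
- *True effect −1.2 at 12 months, half present at 6 months, no drift.* At 30% missing: 0.70 × (−1.2) + 0.30 × 0.5 × (−0.6) = −0.93. With baseline only carried in both arms: 0.70 × (−1.2) = −0.84. At 20% missing the figures are −1.02 and −0.96. The 6-month score lessens the attenuation.

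**The case against.** The strongest reply is that the size is conditional and often small. With no mean change the bias is zero. The documents report no HADS trend, and Study population sets no HADS threshold for entry, so eligibility does not select on high scores and build in regression to the mean. A common 2-point fall would exceed the target effect, which is 0.298 × 4 = 1.2 points under the assumed SD. Just above the 10% trigger, with a 1-point fall, type I error hardly moves. All of this stands, and it limits the severity.

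The sentence also sits among CSQ sentences, so it may have been meant only for the CSQ. That is possible, but nothing in the text restricts it, and the next sentence extends the methods described above it to CSQ and CollaboRATE. The named mixed model could use observed data without imputation, but the primary result comes from the t-test on change.

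Four stronger readings are tempting and not supported:

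- That the rule always biases the comparison. It needs a mean change over time, and the terms can cancel.
- That the schedule difference causes the large error rates under unequal dropout, or the shrinkage of a true effect. The comparisons above put most of the first, and all of the second, down to carrying forward as such.
- That CSQ and CollaboRATE share the asymmetry. Both arms complete them at the same two times.
- That the analysis is picked to suit the results. The trigger is a missing rate fixed in advance, not an outcome or a p-value.

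**Conclusion.** The point holds in conditional form. As written, the carry-forward rule imputes different quantities in the two arms for the primary outcome, and equal, completely random missingness does not cure this. With no treatment effect the bias is m·q times the common 6-month change. It favours the intervention if scores fall, works against it if they rise, and vanishes if they stay flat.

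Under the assumed inputs the size runs from negligible (about -0.07 points, type I error 5.5 to 6%) to material (about -0.3 points, 15 to 18%). Where the trial falls in that range depends on drift, missingness and 6-month completion, none of which the documents give. The Discussion itself names continued participation as a limitation, so missingness above 10% is plausible. Ordinary carry-forward error under unequal dropout, and its usual attenuation of a true effect, are further reasons to drop the method but are separate from the schedule problem. Severity: should-fix.

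**What to change.** For HADS, delete the carry-forward sentence and its 10% trigger. Estimate the 12-month difference in change for HADS-A and HADS-D from the observed baseline and 12-month scores of all randomised patients, using the likelihood-based linear mixed model the plan already names. Include arm, time and arm by time, without covariates selected for significance. This is valid under missing at random. If carrying forward is kept at all, confine it to a sensitivity analysis. For CSQ and CollaboRATE the same model may be used for consistency, but the asymmetry does not require it.

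The cost is revised wording and a little programming, with no new data. The primary t-test is replaced by a model-based contrast. With complete data at the two time points, that contrast estimates the same difference in mean change, so the estimand and the sample size basis do not change.

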### Data analysis

Prior to conducting statistical analysis, preliminary screening will be conducted using Statistical Analysis System (SAS) 9.4 software (SAS Institute Inc, Cary, NC, USA) to ensure that all the enrolled patients meet the eligibility inclusion and exclusion criteria and confirm the participants provide informed consent. Data assessors will be blinded to participant intervention versus conservative grouping status via de-identified data.

Data analysis will be performed using the computer R 3.4.0 software (Vienna, Austria; https://www.R-project.org/) and SAS 9.4 software. Patient demographic and clinical characteristics will be analysed using descriptive statistics. Categorical variables will be reported using frequency, and percentage and continuous variables will be reported using mean (standard deviation [SD]) or median (interquartile range [IQR]) as appropriate. Univariate level analysis will be conducted to determine if there is a statistical significance between the outcomes (e.g., baseline to six months and 12 months, respectively). Chi-square and Independent T-tests will be used for the univariate analysis, or where appropriate, non-parametric tests (Fishers test and Wilcoxon rank test) will be utilized. Multivariate analysis of variance (MANOVA) will be used to test for overall differences between the intervention and conservative groups at the different time points and variances amongst the variables by groups and time points. All test assumptions will be checked during the data analysis process. Statistical significance will be set at *p* values less than 0.05.

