Providers will additionally need to determine how to incorporate data gathered from PROMs, critical alerts, and the 3IP into their daily workflow and patient management; consequently, uptake and utilization of PROM information into day-to-day practice by individual providers may be heterogenous. The use of PROMs may work better when integrated directly into the patients’ electronic medical records system (EMR). Different Alberta clinics use different electronic medical records systems, and the functionality of integrating such PROMs prompts into each EMR system was beyond the scope of this study, as we wished to examine the utility of regular PROM use in different outpatient MS health provider settings (ie: tertiary MS clinic, community MS clinic, private practice neurologists’ offices). Therefore, there may be an extra step in opening up the EMR chart for the patients for the healthcare providers when receiving a secure email alert about completion of PROMs. Furthermore, survey administration, data collection, and alert notification via REDCap on a digital-only format aids in execution of our study, but potentially may limit accessibility and enduring follow-up for less technologically-savvy participants.

In conclusion, this randomized controlled trial will explore the feasibility of incorporating systematic PROM completion by patients and hopefully, will build on the existing communication channels between MS healthcare providers and PwMS. Finally, this study will evaluate whether the systematic collection of PROMs enhances or alters depression or anxiety levels in PwMS. This study will also secondarily examine the influence of regular implementation of PROMs on the perception of provider satisfaction and shared decision making by PwMS, and resultant qualitative provider responses and interventions on the utility and feasibility of PROMs in their MS practice. The results of this study may add to the growing literature focused on PROMs in PwMS, and delineate the practicality of their use with both PwMS and their healthcare providers.

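### Covariates for the supportive mixed model must be univariately significant in the trial's own data, so prognostic variables can drop out by chance and the adjusted estimate depends on the sample

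*Protocol article*

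**What the plan says.** All of this is in the protocol article.

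- **Model.** Data analysis: "Linear mixed effect model will be used in multivariable analysis level in order to adjust patients’ individual effect". It is to describe change over time and between the groups, reported as coefficients with standard errors, confidence intervals and p-values.
- **Entry rule.** Data analysis: "The variables included in the multivariable analysis will be selected if they were statistically significant on the univariate level analysis", and the sentence goes on "and considered clinically significant by the research team". A variable must meet both conditions. The article gives no candidate list and no date for the clinical judgement.
- **Threshold and screening tests.** Data analysis sets significance at p "values less than 0.05" and states: "Chi-square and Independent T-tests will be used for the univariate analysis", with non-parametric alternatives.
- **Primary test.** Data analysis: the change in HADS-D and HADS-A from baseline to 12 months, "between the intervention and conservative groups, will be tested using an independent T-test". Sample size is worked out for that test, under "assumptions of 80% power and a two-sided alpha of 0.05".
- **Provider.** Each patient selects a provider at registration and is placed in that provider's Data Access Group (Patient enrolment). The Discussion expects that "uptake and utilization of PROM information into day-to-day practice by individual providers may be heterogenous".

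**The concern.** In a randomised comparison, adjustment covariates earn their place by being prognostic, which is known from clinical knowledge before the data arrive. A p-value from the same trial is a poor substitute, because it mixes the strength of the covariate with chance. Since significance is a necessary condition here, the clinical judgement can only remove variables. It cannot rescue an important one that reached, say, p = 0.07.

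Two things are at stake. First, the content of the adjusted model, and so the adjusted group estimate, would differ between repetitions of the same trial. Second, because neither the candidates nor the timing of the clinical judgement is stated, the final list could be settled after results are known. Readers will take this model as the adjusted treatment effect, so its content should not be in doubt.

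**Working it through.** **1. The plan's own figure.** Inputs from Sample size: standardised difference 0.298 (read as standardised, since no SD is given), two-sided alpha 0.05, power 80%. The normal approximation gives n per arm = 2 × (1.960 + 0.842)² / 0.298² = 176.8, so 177. The exact t-test gives 177.7, so 178 per arm and 356 in total, as stated. The checks below use N = 356.

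**2. Chance that a real predictor fails the screen.** For a true correlation r with the outcome, P(fail) = Φ(1.96 − atanh(r) × √(N − 3)), with √353 = 18.79. For a two-level covariate the t-test is a test of this same correlation. The values of r are assumed.

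| r | atanh(r) × 18.79 | P(fail) |
|---|---|---|
| 0.10 | 1.885 | 53% |
| 0.15 | 2.840 | 19% |
| 0.20 | 3.809 | 3% |

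**3. What that does to the model.** With three independent predictors, each at r = 0.15, all three survive with probability 0.81³ = 0.53. The same trial repeated would then fit an incomplete model in about 47% of cases.

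**4. What is lost per variable.** Adjusting for a covariate multiplies the outcome variance by about 1 − r²: 0.990 at r = 0.10, 0.978 at 0.15 and 0.960 at 0.20. The variables most often dropped are those that cost least. The loss of precision is therefore small for each variable, and the larger defect is that the model is not fixed.

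**5. Type I error.** This was simulated with N = 356, ten candidate covariates (three prognostic, coefficient 0.2 each), no group effect, and a linear model of change on group plus the selected covariates.

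- Covariates fixed in advance: 5.1% (6,000 runs).
- Screen at 0.05 applied mechanically: 4.8% (6,000 runs).
- Worst case, taking whichever subset of the screened variables gives the largest group statistic: 8.7% (4,000 runs).

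The simulation standard error near 5% is √(0.05 × 0.95 / 6,000) = 0.3 percentage points, so the first two figures do not differ meaningfully from 5% or from each other.

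**6. Irrelevant variables.** For k independent candidates of no prognostic value, the chance that at least one passes the significance condition is 1 − 0.95^k: 23%, 40% and 64% for k = 5, 10 and 20. These are upper bounds on entry, because the clinical condition must also be met, and k is assumed.

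**The case against.** The strongest reply is that this is a supportive analysis. The primary test, on which the trial is sized, uses no covariates. The clinical condition keeps implausible variables out. An irrelevant baseline variable that does get in costs about one degree of freedom and does not bias a randomised contrast. Data assessors are to be blinded to group, and an analysis plan that is not shown may list the candidates. All of this stands and limits the weight of the point. It does not remove it: the article fixes significance as a necessary condition, and does not say that the clinical judgement is made while blinded.

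A reader might infer more than the documents support:

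- **Noise chooses the model, or the reported intervals and p-values have no valid error rate.** The 23%, 40% and 64% ignore the clinical condition, and mechanical screening gave 4.8%. The 8.7% requires choosing the subset after seeing results, which the article does not plan.
- **Baseline HADS will be left out.** In a mixed model of change over time, baseline may already be one of the repeated outcomes. If it were instead screened against change, it would fail in at most about 1% of trials (assumed baseline to 12-month correlations 0.5 to 0.9). Only if the screen compares the arms would it fail about 95% of the time, and the article does not make clear which screen is meant.
- **Leaving out provider biases the comparison.** Patients are randomised individually and no stratification by provider is stated, so the contrast is not biased. Stable provider differences would largely be absorbed by the patient effect. The varying uptake described in the Discussion concerns how the intervention works, and a provider random intercept would not model that.

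**Conclusion.** The point holds as a moderate one about the supportive adjusted model. The stated rule can drop clinically important prognostic variables by chance: about 53% of the time at a true correlation of 0.10 and 19% at 0.15, with 356 patients. It also leaves the adjusted group estimate dependent on the sample and open to choice after the fact. The percentages rest on assumed correlations, because the article names no candidates.

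The primary t-test is unaffected. The documents do not support a claim of bias in the randomised contrast, or of type I error inflation from the screen itself.

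**What to change.** In Data analysis, delete the univariate-significance condition. Before unblinding, list the adjustment covariates by name, chosen on clinical and prognostic grounds, and state that they stay in the model whatever their p-value.

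State how the baseline value of the outcome enters, and let it enter once. There are two options:

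- as a covariate, with only follow-up values as outcomes (12 months is the only follow-up at which both arms are measured); or
- as one of the repeated outcomes, with a common baseline mean across arms.

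Doing both would use it twice. Site or provider, already recorded through the Data Access Group, may be added as a pre-named term for precision.

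The cost is wording and slight analysis work. No new data are needed, and the stated 356 is unchanged because it was derived for the t-test.
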